# Assessment of Truflex™ articulating stylet versus conventional rigid Portex™ stylet as an intubation guide with the D-blade of C-Mac™ videolaryngoscope during elective tracheal intubation: study protocol for a randomized controlled trial

**DOI:** 10.1186/1745-6215-14-298

**Published:** 2013-09-16

**Keywords:** Videolaryngoscope, Tracheal intubation, Truflex stylet

## Abstract

**Background:**

A variety of videolaryngoscopes with angulated blade have been recently introduced into clinical practice. They provide an indirect view of the glottic structures in normal and challenging clinical settings. Despite the very good visualization of the laryngeal structures by these devices, the insertion and advancement of the endotracheal tube may be prolonged and occasionally fail as it does not conform to the enhanced angulation of the blade. To overcome this handicap, it is recommended to use a pre-shaped, styleted tracheal tube during intubation. Unfortunately, these malleable rigid stylets permit only a fixed shape to the advancing endotracheal tube. This may necessitate withdrawal of endotracheal tube-stylet assembly for reshaping, before undertaking a new attempt. This may cause soft tissue injury and hemodynamic disturbance.

This single-blinded randomized clinical trial aims to overcome these handicaps using a novel method of dynamically changing the shape of the advancing endotracheal tube by Truflex™ articulating stylet as per need during D-blade C-Mac™ videolaryngoscopy.

**Methods:**

One hundred and fifty four patients between 18 and 60 years of age belonging to either sex undergoing tracheal intubation under uniform general anesthetic technique will be randomly divided into Portex™ malleable stylet group and Truflex™ articulating stylet group. The primary efficacy variable of success/failure between the two groups will be analyzed using the chi square test. For comparison of intubation times and the Intubation Difficulty Score, ANOVA will be used. Primary efficacy endpoint results will be successful or failed tracheal intubation in the first attempt, total intubation time and the intubation difficulty score. Secondary efficacy endpoints will be overall user satisfaction graded from 1 to 10 (1 = very poor, 10 = excellent), Cormack and Lehane’s grading, glotticoscopy time and ETT negotiation time and total number of intubation attempts. Result of safety endpoints will include dental and airway trauma, hemodynamic disturbances, arrhythmias or cardiac arrest.

**Trial registration:**

Current Controlled Trials ISRCTN57679531; Date of registration 12/02/2013

## Background

Videolaryngoscopes now play an important role as an alternative to conventional rigid laryngoscopy. A major advantage of the videolaryngoscope is better visualization of the larynx [1,2]. This is achieved as a result of increased angulation of the blade compared to the standard Macintosh blade (Figure 1a). Videolaryngoscopes provide an indirect view of the laryngeal structures on the screen compared to the traditional Macintosh laryngoscope, which necessitates in-line visualization of the glottis using the naked eye for successful tracheal intubation. Videolaryngoscopes serve as a valuable teaching aid as they display the laryngeal structure on a video screen [3-6]. Both reusable and disposable versions are now available.

**Figure 1 F1:**
[figure not shown]
**Enhanced angulation of the D-blade of the C-Mac™ videolaryngoscope. (a)** Shown is the sharper blade angulation of the D-blade of the C-Mac™ videolaryngoscope versus the conventional Macintosh laryngoscope blade. **(b)** The natural curvature of the traditional endotracheal tube does not match the enhanced angulation of the D-blade of the C-Mac™ videolaryngoscope.

Despite several advantages offered by the videolaryngoscopes, their major handicap is their enhanced anterior angulation of the blades, such as that of the Glide-Scope™ (Verathon Medical, Bothell WA, USA), the McGrath series 5 (Aircraft Medical, Edinburgh, UK), and the TruView™ PCD devices (Truphatek International Limited, Netanya, Israel), which makes viewing of the laryngeal structure easier [1,2], but negotiation of the endotracheal tube (ETT) towards the glottis difficult, and at times a failure [7,8]. This is attributed to the fact that the tip of the ETT has to pass around the steep angle of the videolaryngoscope blade to site with the larynx. An un-styleted ETT is unable to do this as its inherent radius of curvature of nearly 14 cm [9] cannot align with the acute radius of curvature of the D-blade of the C-Mac™ or other videolaryngoscopes, which is 7 to 8 cm (Figure 1b). This may result in a longer intubation time [10]. It is recommended that a pre-shaped, styleted tube be used during endotracheal intubation with a videolaryngoscope to overcome this problem [11]. The Glide-Scope™ and TruView™ PCD have their own pre-shaped dedicated rigid stylets, which do not permit reshaping. Unfortunately, the pre-shaping of the ETT with a stylet may not always suit an individual patient’s need [12]. In such a patient, if the stylet permits, such as the malleable Portex™ intubation stylet (PIS) (Smiths Medical ASD, Inc. Norwell, MA, USA], the ETT-stylet assembly has to be taken out and re-shaped before making another attempt at tracheal intubation. This may delay endotracheal intubation with a potential increased hemodynamic response and soft-tissue trauma [13,14].

The present trial (ISRCTN57679531) aims at utilizing the Truflex™ articulating stylet (TAS) (Truphatek) as a dynamic aid to tailor the ETT shape in its very first attempt as per the videolaryngoscope blade design (Figure 2) and the patient’s oropharyngeal anatomy. We hypothesize that a pre-loaded ETT over the TAS will not only shorten the D-blade C-Mac™ videolaryngoscope-aided intubation time, but will also attenuate the hemodynamic response and reduce the possibility of soft-tissue trauma, both in patients with normal anatomy and in those whose anatomy makes access more difficult, compared to non-dynamic PIS-aided tracheal intubation.

**Figure 2 F2:**
[figure not shown]
**Advantage of the Truflex™ articulating stylet.** The shape of the endotracheal tube has been changed to conform to that of the D-Blade using the Truflex™ articulating stylet.

## Methods

The study protocol has been approved by the Ethical Issues Committee, Khoula hospital. The current study is an interventional, single-blinded, parallel assignment, randomized controlled trial. The aim of the study is to compare the conventional rigid Portex™ stylet with the Truflex™ articulating stylet as an intubation guide during videolaryngoscopy. Stratified block randomization with variable block sizes will be done (Figure 3). The freeware Random Allocation software of Mahmood Saghaei will be used for generating randomization sequences [15]. Stratification will be based on anticipated difficulty in intubation based on the anticipated difficulty airway (ADA) score (Table 1). Sealed opaque envelopes will be used for allocation concealment with sequential numbering within each stratum. For randomization the envelopes will be opened only after transporting the patient to the operating theater, thus, maintaining allocation concealment and only one envelope can be opened per patient.

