Patients between 18 and 60 years of age, of either sex, graded I or II according to the criteria of the American Society of Anesthesiologists, undergoing elective surgical procedure under general anesthesia and tracheal intubation, and who give written informed consent, will be included. Patients with known airway pathology, previous ear, nose and throat (ENT) surgery of the oropharynx, known malignancies prior to randomization, immobilized cervical spine, known allergies to either study devices or its components, pregnancy, or known bleeding/coagulation disorder, will be excluded from the study. Patients will undergo a uniform induction technique with propofol 2.0 to 2.5 mg/kg and adequately relaxed with either cisatracurium 0.1 mg/kg or rocuronium bromide 0.6 mg/kg as evident by loss of all train of four responses using a peripheral nerve stimulator (Innervator Constant Current Peripheral Nerve Stimulator, Fisher & Paykel Health Care System, New Zealand). With the induction of anesthesia, patients shall also be administered 1.5 μg/kg of fentanyl. For patients in group A, a well-lubricated PIS (Figure 4a) will be used to shape the ETT according to the curvature of the videolaryngoscope D-blade. This pre-shaped ETT will be guided into the trachea after obtaining an adequate view of the glottis of an anesthetized and fully relaxed patient using the C-Mac™ D-blade videolaryngoscope. For patients in group B, a well-lubricated TAS (Figure 4b) will be used in place of the rigid stylet to change the curvature of the ETT as per need to negotiate into the glottis, using the same videolaryngoscope. In both groups, videolaryngoscopy and tracheal intubation will be done by an experienced anesthesiologist. An experienced anesthesiologist will be defined for the purpose of this study as an operator performing at least 300 videolaryngoscopies per year at a center with a case load of at least 500 videolaryngoscopies per year.

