**Figure 4 F4:**
[figure not shown]
**Stylets used in the intervention arms. (a)** Conventional Portex™ intubation stylet used in group A patients. **(b)** Truflex™ articulating stylet with stopper used in group B patients.

Primary efficacy endpoints will be successful or failed tracheal intubation in the first attempt, total intubation time and the intubation difficulty score. An attempt will be counted if the laryngoscope or the ETT needs to be removed for re-oxygenation (drop in oxygen saturation by 5%) or for reshaping of the ETT. The total intubation time will be the sum of the glotticoscopy time (from introduction of the videolaryngoscope blade between the teeth to the best laryngeal view) and the ETT negotiation time (from receiving the styleted ETT in laryngoscopist’s hand to passage of the black line just beyond the vocal cord). Secondary efficacy endpoints will be overall user satisfaction graded from 1 to 10 (1 = very poor, 10 = excellent), Cormack and Lehane’s grading, glotticoscopy time and ETT negotiation time and total number of intubation attempts with a maximum of three attempts, after which an alternative technique will be used. Safety endpoints assessed will be dental and airway trauma (present or absent), hemodynamic disturbances (blood pressure and pulse rate would be recorded before intubation, 1 minute and 5 minutes post-intubation; ≥20% change from the baseline value will be considered clinically important), arrhythmias (absent or present; type if present), or cardiac arrest.

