## Discussion

The last decade has seen the emergence of videolaryngoscopes that enable us to visualize the laryngeal structures on a high-resolution video screen. These new aids provide a superior view of the laryngeal structures in normal conditions, and in a plethora of pathological and challenging conditions. However, the negotiation of the ETT into the trachea may still be a challenge despite using a malleable rigid stylet to pre-shape the ETT. In such situations, if the pre-shaping has not been optimal, the ETT-rigid stylet assembly needs to be taken out of the oropharynx for re-adjustment of its shape before making another attempt at tracheal intubation.

To overcome the limitation of a malleable rigid stylet, Schroeder’s directional stylet has been used to guide the ETT towards the glottis while using the D-blade of the C-Mac™ videolaryngoscope [12]. However, Schroeder’s directional stylet has two limitations. First, its length is not sufficient, especially for the armored ETT to be fully mounted over it, and second, it helps to change the shape of the premounted ETT into a C shape rather than a curvature at its distal end where it is actually needed. In contrast, the TAS has sufficient length and its shape can be molded at its distal end to the need of laryngoscopy and tracheal intubation.

TAS is a newly introduced device that has an easily controllable flexible tip using a lever that allows an upward movement of 30 to 60° at its distal 3 cm. The ETT is premounted over a well-lubricated TAS and a stopper at the proximal end of TAS helps to hold the ETT in position (Figure 4b). The TAS permits dynamic shaping of the curvature of the distal end of the premounted ETT by an angle as per need during videolaryngoscopy.

In conclusion, in this clinical trial, we are evaluating the efficacy of TAS in aiding tracheal intubation using the D-Blade of the C-Mac™ videolaryngoscope, using a randomized and single-blinded design. The success of the trial will significantly improve the application of this relatively new method of tracheal intubation.

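### The single-blind label names no blinded party, and nothing keeps the arm from the operator until the two measures that finish before tube hand-over are recorded

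*Protocol article*

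**What the plan says.** The blinding claim appears three times. The Abstract (Background) has "This single-blinded randomized clinical trial aims to overcome these handicaps", the opening paragraph of Methods has "The current study is an interventional, single-blinded, parallel assignment, randomized controlled trial", and the closing paragraph of the Discussion describes the evaluation as "using a randomized and single-blinded design". None of them names the blinded party.

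On allocation, Methods says that "the envelopes will be opened only after transporting the patient to the operating theater". It does not say who opens the envelope or who sees the content.

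On conduct, the tube is passed "after obtaining an adequate view of the glottis of an anesthetized and fully relaxed patient". The operator uses either a pre-shaped malleable stylet or the articulating one: "TAS is a newly introduced device that has an easily controllable flexible tip using a lever" (Discussion).

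The endpoint paragraph of Methods defines total intubation time as glotticoscopy time plus tube negotiation time. Glotticoscopy time runs from blade insertion to the best view of the larynx. Negotiation time runs "from receiving the styleted ETT" until the tube's black line has passed the cords. The Cormack-Lehane grade is a secondary endpoint. On safety the paragraph reads "Safety endpoints assessed will be dental and airway trauma (present or absent"), followed by hemodynamic changes, arrhythmia and cardiac arrest. No recorder is named for any endpoint.

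**The concern.** A blinding label tells the reader which measurements are protected from knowledge of the arm. Here the patient is under general anesthesia and supplies no endpoint, and the person using the stylet cannot be blind while using it. If the label refers to the patient, it protects none of the listed outcomes. If it refers to someone else, the article does not say so.

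Several endpoints involve operator judgment. One is when the best view has been reached. Another is whether the tube must come out for reshaping, which counts as an attempt. The difficulty score and the satisfaction rating are others. The Background hypothesizes that the new device shortens intubation time, so the timing endpoint carries part of the main claim.

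Most of this exposure cannot be avoided in a device trial. One part can: the glotticoscopy phase ends before the stylet plays any role, yet the operator may already know the arm during it.

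**Working it through.** **1. Related figures in the plan.** Nothing in the protocol quantifies blinding. The nearest number is the sample size in Statistical considerations: 154, raised to 158, for 90% versus 100% first-attempt success at 80% power and two-sided 0.05. With the Kelsey formula, n per arm = (1.96 + 0.8416)² × 2 × p̄(1 − p̄) / d².
- With 100%: p̄ = 0.95, d = 0.10, so 7.849 × 0.095 / 0.01 = 74.6, giving 75 per arm and 150 in total.
- With 100% entered as 99.9% (an assumption): p̄ = 0.9495, d = 0.099, giving 77 per arm and 154 in total.

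The figure is reproduced within rounding of the input. It does not depend on who is blinded.

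**2. When the operator must know the arm.** Setting the endpoint definitions beside the sequence of the procedure:

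| Endpoint | Complete before the tube is received? | Operator can be masked? |
|---|---|---|
| Glotticoscopy time (component of a primary endpoint) | Yes | Yes, if the tube is prepared out of sight |
| Cormack-Lehane grade | Yes | Yes, same condition |
| Negotiation time | No, it starts at receipt | No |
| First-attempt success, number of attempts | No | No |
| Intubation difficulty score | No | No |
| User satisfaction | No, it rates the device | No |

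The negotiation clock starts when the laryngoscopist receives the tube, which implies that another person hands it over. Masking up to that moment therefore fits the sequence the protocol already uses.

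**3. How a shift in glotticoscopy time reaches the primary endpoint.** Let T = G + N for total, glotticoscopy and negotiation time. The between-arm mean difference is D(T) = D(G) + D(N). The stylet plays no part in G, so apart from chance D(G) should be zero. If knowing the arm shifts G by b seconds on average in one arm, the expected D(T) is the expected D(N) plus b. The shift carries over one for one, and the 95% interval for the mean difference moves with it. The article gives no means or standard deviations for these times, so b and its effect on the error rate cannot be calculated.

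The interval between best view and receipt of the tube belongs to neither G nor N. Recording the grade there adds nothing to the primary time.

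**4. Illustrations of unmasked recording (assumed rates; not about glotticoscopy).** The article gives no trauma rate. The table uses 79 per arm (158 / 2), equal true trauma in both arms, and a stated fraction of events recorded in the Truflex arm only. It gives the exact probability of rejection by uncorrected chi-square at 0.05.

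| True trauma rate | All recorded | 70% recorded | 50% recorded |
|---|---|---|---|
| 5% | 5.0% | 7.1% | 11.9% |
| 10% | 5.2% | 10.6% | 22.8% |
| 20% | 5.2% | 17.5% | 43.3% |

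If Fisher's test is used whenever an expected count is below 5, the 5% row becomes 2.9%, 3.4% and 5.3%, which is essentially no inflation. With 90% recorded at a 10% true rate, chi-square rejection is 5.7%.

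For first-attempt success, suppose 4 failures in each arm become 12 versus 4 through 8 extra discretionary withdrawals in the Portex arm. Chi-square = 158 × (12 × 75 − 4 × 67)² / (79 × 79 × 16 × 142) = 4.45, p = 0.035; Fisher's exact p = 0.062. All expected counts are at least 8, so chi-square would apply. The 8 withdrawals are an assumption, and this endpoint cannot be masked in any case.

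**The case against.** The strongest reply is that this is a journal article. Who records each outcome, and whether they are masked, is commonly left to the full protocol, which is not shown. The label may also be formally true of the patient. That stands: failing to name the blinded party or the recorders is missing detail and not in itself an error.

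Three stronger readings are tempting, and the documents do not support them.
- A reader might infer that the patient is the only party who can be blind. The protocol's own sequence shows otherwise: the operator can be masked up to hand-over.
- A reader might infer that the endpoints are in fact recorded with the stylet known. The article is silent on the recorders. It shows only that it contains no provision against this.
- A reader might infer that trauma should be scored by recovery staff and blood pressure and pulse copied from the monitor. Recovery staff appear nowhere in the article, and scoring after surgery and extubation would mix in injury from those sources. The hemodynamic readings are objective values at fixed times with a fixed 20% threshold, so copying them gains little. Neither change is recommended.

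It is also fair to say that the illustrations rest on assumed rates, fade at low event rates, and say nothing about glotticoscopy time. Finally, recruitment had started, so any change falls within a running trial.

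**Conclusion.** The point holds in a limited form. The label is used three times without a blinded party. Patient blinding alone would protect none of the listed endpoints, and the operator is necessarily unblinded from hand-over of the tube. The avoidable part is glotticoscopy time and the Cormack-Lehane grade. Both are finished before hand-over, and the article has no provision keeping the arm from the operator until then.

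The size is unknown. A shift in glotticoscopy time enters the primary total intubation time one for one, but no timing data are given from which to estimate it. The trauma and first-attempt calculations show only what could happen under assumed rates and are not evidence of bias in this trial. The conclusion assumes that the operator can be kept from seeing the tube until it is handed over. This is a cheap improvement, not a flaw that undermines the trial.

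**What to change.** 1. In Methods (the randomization text and the endpoint paragraph), add that an assistant opens the envelope and prepares the styleted tube out of the operator's sight. The operator declares the best view, the glotticoscopy clock is stopped and the Cormack-Lehane grade is recorded, and only then is the tube handed over.
2. In Methods (design statement) and the closing paragraph of the Discussion, say who is blinded and that the operator is unblinded from hand-over. State that first-attempt success, negotiation time, difficulty score and user satisfaction are therefore read as unblinded measures.

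The cost is a few sentences and a small change in workflow, with no change to the sample size or the analysis. There are two small downsides. The assistant, not the operator, prepares the tube, including the pre-shaping in the Portex arm; the article does not say who does this now. In addition, the 11 patients recruited by submission (Trial status) may have been handled differently, so the date of the change should be recorded.

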**Figure 3 F3:**
[figure not shown]
**Scheme of stratified randomization.** After appropriate exclusions all eligible patients will undergo airway assessment with the ADA score and stratified into easy and difficult airway strata, and will then be randomized into the two treatment groups. ADA, anticipated difficult airway; PIS, Portex™ intubation stylet; TAS, Truflex™ articulating stylet.

**Table 1 T1:** **Anticipated difficult airway (ADA) score**^*****^

**Airway factors**	**Score**		
	**0**	**1**	**2**
**Mallampati classification**	Class I	Class II	Class III to IV
**Thyromental distance, cm**	>6.5	6.0 to 6.5	<6.0
**Head and neck movement, degrees**	>90	90	<90
**Body mass index, kg/m**^**2**^	<25	≥25	NA
**Buck teeth**	No	Mild	Severe
**Inter-incisor gap, cm**	>5.0	4.0 to 5.0	<4.0

^*^Easy airway strata: ADA score ≤6; difficult airway strata: ADA score >6; NA- Not applicable.

Patients between 18 and 60 years of age, of either sex, graded I or II according to the criteria of the American Society of Anesthesiologists, undergoing elective surgical procedure under general anesthesia and tracheal intubation, and who give written informed consent, will be included. Patients with known airway pathology, previous ear, nose and throat (ENT) surgery of the oropharynx, known malignancies prior to randomization, immobilized cervical spine, known allergies to either study devices or its components, pregnancy, or known bleeding/coagulation disorder, will be excluded from the study. Patients will undergo a uniform induction technique with propofol 2.0 to 2.5 mg/kg and adequately relaxed with either cisatracurium 0.1 mg/kg or rocuronium bromide 0.6 mg/kg as evident by loss of all train of four responses using a peripheral nerve stimulator (Innervator Constant Current Peripheral Nerve Stimulator, Fisher & Paykel Health Care System, New Zealand). With the induction of anesthesia, patients shall also be administered 1.5 μg/kg of fentanyl. For patients in group A, a well-lubricated PIS (Figure 4a) will be used to shape the ETT according to the curvature of the videolaryngoscope D-blade. This pre-shaped ETT will be guided into the trachea after obtaining an adequate view of the glottis of an anesthetized and fully relaxed patient using the C-Mac™ D-blade videolaryngoscope. For patients in group B, a well-lubricated TAS (Figure 4b) will be used in place of the rigid stylet to change the curvature of the ETT as per need to negotiate into the glottis, using the same videolaryngoscope. In both groups, videolaryngoscopy and tracheal intubation will be done by an experienced anesthesiologist. An experienced anesthesiologist will be defined for the purpose of this study as an operator performing at least 300 videolaryngoscopies per year at a center with a case load of at least 500 videolaryngoscopies per year.

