### Statistical considerations

For sample size assessment, a pilot study of 60 patients was conducted in which we observed that successful intubation could be achieved in the first attempt in 100% (30/30) of patients in group B (TAS) but was achieved in 90% (27/30) of group A (PIS). To detect a similar difference between the success of intubation (100 versus 90%) with a statistical power of 80% and 95% confidence interval and equal distribution of patients in both the groups, a total sample size of 154 was estimated for the present study using the open source browser-based calculator OpenEpi [16]. However, in light of the stratification used for randomization the final sample size of 158 shall be used with equal distribution. All statistical evaluations will be made at a significance level of 0.05 (two-sided). A two-sided, 95% confidence interval will be calculated for the mean difference between the treatment groups. The data will be analyzed on an intention-to-treat basis. No imputations will be used for any missing data. The primary efficacy variable of success/failure between the two groups will be analyzed using the chi square/Fisher’s exact test, whichever will be applicable. Binary logistic regression will also be used on the whole dataset to identify predictors of success/failure of intubation. For evaluation of intubation times and the intubation difficulty score, analysis of variance (ANOVA) will be used for comparison between both treatment groups. The intubation difficulty scale (IDS) will also be transformed into an ordinal variable (0, 0 to 5, >5) and multinomial logistic regression will be used to evaluate for possible predictors of a difficult intubation.

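### If more than one anesthesiologist intubates, the operator can be settled after the arm is known, and the named treatment comparisons carry no operator or ADA-stratum term

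*Protocol article*

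**What the plan says.** The Methods section of the protocol article sets one operator rule for both arms: "In both groups, videolaryngoscopy and tracheal intubation will be done by an experienced anesthesiologist". Experience is defined as "an operator performing at least 300 videolaryngoscopies per year at a center with a case load of at least 500 videolaryngoscopies per year". Nothing else restricts who performs a given case, and the number of operators is not stated.

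The same section fixes when the arm becomes known: "For randomization the envelopes will be opened only after transporting the patient to the operating theater". Randomization is stratified on one factor, the ADA score (easy stratum up to 6, difficult stratum above 6). Operator is not a stratum.

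Statistical considerations names the treatment comparisons. For first-attempt success: "The primary efficacy variable of success/failure between the two groups will be analyzed using the chi square/Fisher’s exact test, whichever will be applicable". For intubation times and the difficulty score: "analysis of variance (ANOVA) will be used for comparison between both treatment groups". Neither mentions operator or ADA stratum. A further model is planned, "Binary logistic regression will also be used on the whole dataset to identify predictors of success/failure of intubation", and a multinomial model for the categorised difficulty scale. Their predictors are not listed.

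**The concern.** Opening sealed envelopes late protects which patient gets which stylet. It does not protect which operator gets which stylet. If two or more anesthesiologists qualify, a team that follows the article to the letter can still decide who intubates after seeing the allocation.

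The operator matters for all three primary endpoints. First-attempt success turns partly on the operator's decision to withdraw the tube for reshaping, both components of total intubation time are in the operator's hands, and the difficulty score describes the same intubation. The operator also cannot be blinded to the stylet in use.

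Two different consequences are possible, and they are alternatives:

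- Operator choice follows the arm: operator differences enter the treatment effect as bias.
- Operator is independent of arm: there is no bias, but operator variation sits in the error term of the unadjusted ANOVA and costs some power. Leaving out the ADA stratum, on which randomization is balanced, has the same effect.

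**Working it through.** **Inputs from the article.** Planned first-attempt success is 100% (articulating stylet) against 90% (rigid stylet), with two-sided alpha 0.05, 80% power, 154 patients raised to 158, hence 79 per arm.

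**Assumed inputs.** The article gives no operator success rates, case shares or variance shares. Those below are illustrations.

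**The plan's own figure.** n per arm = (1.960 + 0.842)² × 2 × 0.95 × 0.05 / 0.10² = 74.6, so 75 per arm and 150 in total. Entering 99.9% for 100% gives 76.8, so 77 per arm and 154. The stated 154 reproduces, and this point does not rest on a sample-size error.

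**Bias when operator follows arm.** With two operators and no stylet effect,

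spurious difference = (success gap between operators) × (difference in the better operator's share of the two arms).

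- 8-point gap: 8 × 0.20 = 1.6 points; 8 × 0.30 = 2.4 points.
- 10-point gap: 10 × 0.20 = 2 points; 10 × 0.30 = 3 points.
- Full alignment (share difference 1): 8 or 10 points.

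**False rejection.** Exact Fisher test, 79 per arm, two-sided 0.05, no stylet effect, operator case counts fixed at the nearest whole patient:

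| Better operator's share, arm 1 / arm 2 | 98% and 90% | 100% and 90% | 98% and 88% | 95% and 85% |
|---|---|---|---|---|
| 50 / 50 | 1.7% | 1.3% | 1.9% | 2.6% |
| 60 / 40 | 2.7% | 2.9% | 3.4% | 3.8% |
| 65 / 35 | 4.1% | 5.3% | 5.5% | 5.5% |
| 75 / 25 | 9.3% | 15.5% | 13.6% | 11.9% |
| 100 / 0 | 43.5% | 81.4% | 61.3% | 47.4% |

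Fisher's test is conservative here (1.3% to 2.6% with equal shares). A 20 to 30-point share difference therefore uses up its margin but leaves false rejection at about 3% to 5.5%. With a smaller gap (97% and 93%), a 75/25 split gives 2 points and 3.3%, and full alignment gives 4 points and 10.3%.

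**Bias under the planned effect.** If the articulating stylet truly succeeds in 100%, operators cannot differ in that arm. With rates of 95% and 85% in the rigid-stylet arm and equal shares, that arm's rate is 90%. If the better operator does 40% of that arm, it is 0.40 × 95 + 0.60 × 85 = 89%; at 35% it is 88.5%. The bias is then 1 to 1.5 points, half the figure above.

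**Precision when operator is independent of arm.** If operators explain a share r of the variance of a continuous endpoint, adjusting is worth 1/(1 − r) times the patients: 1.11, 1.25 and 1.43 for r = 0.10, 0.20 and 0.30. Two-sample t power at 79 per arm for an assumed difference of 0.4 SD, with effect 0.4/√(1 − r), rises from 70.5% to 75.0%, 79.8% and 84.8%.

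**The case against.** The strongest reply is that this is silence in a condensed article. The roster, the time at which the operator is named and the model covariates may all stand in the full protocol or analysis plan. Much of that is fair: the article does not show that bias will occur, and the full protocol may already fix the operator. What remains is that the article does state the operator rule, the moment of unveiling, the single stratification factor and the comparisons. Taken together, these leave the gap open.

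Other parts of the reply stand in full:

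- **Number of operators.** With one operator for all patients, the operator part disappears. A reader might infer from the volume thresholds that operators are few, since 2 × 300 = 600 exceeds 500. The inference fails: 500 is a minimum for the centre and puts no upper limit on operators. Were it the actual load, it would leave room for only one.
- **Swapping after allocation.** A reader might infer that operators will be chosen by arm. The article permits this but nowhere describes it.
- **Operator ignored altogether.** This is too strong. The regression predictors are unlisted, so operator could be among them. Those models search for predictors, however, and are not the stated treatment comparison.
- **Magnitude.** Every operator gap and share is assumed, and the volume rule may itself narrow the gaps. Moderate imbalance does not push false rejection materially above 5%.
- **Limits of adjustment.** If each operator took exactly one arm, no model could separate stylet from operator. Only fixing the operator beforehand protects against that case.

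**Conclusion.** The point holds as a cheap improvement, conditional on more than one operator. The stated rules allow the operator to be settled after the arm is known, and the named comparisons would neither adjust for operator nor reveal an imbalance.

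Under assumed gaps of 8 to 10 points in first-attempt success, a 20 to 30-point share difference biases the result by about 2 to 3 points (1.6 at the lowest), against a planned difference of 10, and false rejection stays near 5%. It becomes serious at about 75/25 (roughly 9% to 15%) and severe at full alignment (44% to 81%).

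If operator is independent of arm, the treatment estimate is unbiased and the only loss is precision in the ANOVA. The documents do not support a claim that the trial is confounded, or that bias and inflated error arise together.

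**What to change.** 1. Enter the operator's study code in the randomisation log before the envelope is opened, and keep that operator for the study attempts. Where clinicians nevertheless change operator, record it and analyse by the operator first entered.
2. In the ANOVA for times and difficulty score, include ADA stratum and, if there is more than one, operator as factors.
3. Report first-attempt success by operator and arm, and add a treatment comparison stratified by operator (for example Mantel–Haenszel) as a sensitivity analysis beside the planned chi-square/Fisher test.
4. If one anesthesiologist performs all study intubations, say so. The operator items then fall away and only the ADA-stratum term remains.

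The cost is one log entry per patient, one degree of freedom for the two-level ADA stratum and one for each additional operator, out of 158 − 2 = 156 residual degrees of freedom. The sample size does not change. The article reports 11 patients recruited at submission, so nearly all of the trial could still have been covered.
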